### Description of the Intervention

ARAMIS is composed of two computer-controlled, symmetric, and interacting exoskeletons able to compensate for the inadequate strength and accuracy of residual motor function of the paretic arm movements (25) (Figure 1). Through motion capture of the movements of the unaffected arm, the patient can replicate the movements of the healthy arm with the paretic arm in a synchronous, asynchronous, or active-assisted manner (25). Patients in the intervention group will receive only robot-aided and not conventional rehabilitation for a 60 min-session. The robot-assisted neurorehabilitation using ARAMIS and the conventional rehabilitation consists of 60-min sessions every day for 8 weeks (17, 25). In particular, in the first section of neurorehabilitation (1–4 weeks), all the subjects will be subjected to perform a series of asynchronous exercises according to which the paretic limb repeats each exercise 20 times for a total of 200 repetitions per session. During synchronous exercises, the exoskeleton hosting the paretic limb allows the replication of the sample movements of the parallel exoskeleton hosting the unaffected arm in real time. In the asynchronous exercises, the sample movements have been generated previously by the unaffected arm of the patient or by the arm of the therapist. The basic exercises consist in forearm pronation-supination, elbow flexion-extension, shoulder elevation (30°, 60°, and 90°) and abduction-adduction (30°, 60°, and 80°), and circle movement on the frontal axis of the shoulder and its flexion-extension. On the other side, the functional exercise includes: shoulder elevation 90° + forearm pronation-supination and elbow flexion-extension and the contrary (elbow flexion-extension + forearm pronation-supination); shoulder elevation 90° + two elbow intermediate flexion-extension + forearm intermediate pronation-supination. In the following section (5–8 weeks), the asynchronous exercises are reduced to 100 per session and the number of synchronous exercises is increased to keep constant the total number (200/session). The control group will receive conventional rehabilitation. The latter consists of passive mobilization, neuromotor facilitation of shoulder, arm, forearm, and hand muscles and adoption of postures inhibiting pathological synergies in the first 4 weeks. In the following 4 weeks apart from a passive mobilization, neuromotor facilitation, and posture adopting, also the following exercises will be performed: coordination proximal-distal and of ocular-cephalic movements; “reach to indicate”; hand preconfiguration; “reach, touch, and manipulate”; grasping; exercises for manipulative skills, for the adaptation of the hand to the object without visual feedback and the sensitivity, together with biofeedback and electrostimulation cardiovascular conditioning in the sitting posture, conditioning in the upright posture and exercises for the trunk control.

**Figure 1 F1:**
[figure not shown]
Integrated Robotic System for Stroke (IRSS) prototype Automatic Recovery Arm Motility Integrated System (ARAMIS) [reproduced with permission from Pignolo et al. (25)].

In case of discontinuation of the treatment, the patient will be excluded from the study. The treatment will be performed by healthcare operators preventing lack of adherence.

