### Participant Timeline

Patients will be randomly allocated to the intervention or control group in a 1:1 allocation ratio. The enrollment will last up to the achievement of the sample size. The most important time points for the assessment of pain development are 3 and 6 months poststroke, with the addition of measurement time points in the subacute phase (29, 34). In fact, differences in motor activity of paretic limbs 24–36 h after symptoms onset, and also at 3 and 6 months (35, 36) have been demonstrated. Therefore, the assessment of the primary and secondary outcomes will be conducted at the following time points: baseline measurement at Sant'Anna Institute admission (24–72 h since stroke event) (*t*_0_); 1 month after stroke (*t*_1_), i.e., at half of the rehabilitation period; 2 months after stroke (*t*_2_), i.e., after the completion of neurorehabilitation with ARAMIS in the intervention group and of conventional rehabilitation in the nonintervention group; 3 months (*t*_3_) and 6 months (*t*_4_) after stroke, since the latter are critical for rehabilitation and pain development. Routine clinical and neurophysiological assessments will be performed before and at the end of the treatment. Loss of tolerance to the procedure up to discontinuation will be recorded on a specific form. The schedule of enrollment, interventions, and assessments is reported in Table 1.

**Table 1 T1:** Schedule of enrollment, interventions and assessments according to Standard Protocol Items: Recommendations for Interventional Trials (SPIRIT).

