### Sample Size

The calculation of the sample power is based on literature data (25, 36–40) to obtain 25% of improvement in the primary endpoint using G^*^Power 3.1.9.7 (41). The formula for calculating the sample size is given, for two arms of the same size, as it follows:

$$\begin{array}{l} n=\left[{\left(Z_{\alpha /2}+Z_{\beta }\right)}^{2}\times \left(2{\left(\sigma \right)}^{2}\right)\right]/{\left(\mu 1-\mu 2\right)}^{2} \end{array}$$

where,

*n* = sample size required in each group;

*Z*_α/2_ = 1.96, according to 5% level of significance;

*Z*_β_ = 0.84 for 80% power;

σ = standard deviation;

μ1 – μ2 = primary outcome measures significant difference = 6.34 with ARAMIS and 5.4 with conventional rehabilitation (25);

*d* = 0.3.

Therefore, considering a 95% confidence level and a study power of 80% (42), the result will be *n* = 53 per arm.

Adjusted sample size *n*_1_ to account for potential drop-out rates is *n*_1_ = *n*/(1–*d*), where *d* = 10% (43), thus *n*_1_ = 118 patients will be recruited, 59 per each arm.

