### Statistical Analysis

The statistical analysis plan follows the Consolidated Standards of Reporting Trials (CONSORT) evidence-based reporting guideline to ensure research transparency, specifically to trials of nonpharmacologic treatments (NPTs), as rehabilitation (48). The primary (pain) and secondary (spasticity and rehabilitation parameters) outcome measures, collected at prespecified time point *t*_3_ and *t*_4_ vs. *t*_0_, will be expressed as mean and standard error and assessed for statistically significant differences using independent *t*-test for data normally distributed or Mann–Whitney U test for skewed data. Based on the CONSORT NPT item 12b, the evaluation of the outcome measures over time will be carried out through a linear mixed model. The correlation between pain (VAS measure) and recovery (FMA-UE), assessed at *t*_0_, *t*_1_, *t*_2_, *t*_3_, and *t*_4_, will be performed through the Pearson product-moment correlation coefficient (*r*). In agreement with the CONSORT NPT item 12a, the clustering of data will be performed by blinded care providers of the center. Statistical analysis will be performed using SPSS statistics software (Chicago, IL, USA). Values of *p* < 0.05 will be considered statistically significant.

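### Excluding every patient who stops treatment means the 3- and 6-month pain comparison is no longer as randomised and may be selective

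*Protocol article*

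**What the plan says.** At the end of Description of the Intervention (after Figure 1) the protocol article gives an unqualified rule for both arms: "In case of discontinuation of the treatment, the patient will be excluded from the study". The next sentence adds: "The treatment will be performed by healthcare operators preventing lack of adherence".

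Participant Timeline anticipates stopping and names one route to it: "Loss of tolerance to the procedure up to discontinuation will be recorded on a specific form". It also sets out the allocation: "Patients will be randomly allocated to the intervention or control group in a 1:1 allocation ratio".

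Treatment in both arms is "60-min sessions every day for 8 weeks", and Participant Timeline places its end at t2, 2 months after stroke. Statistical Analysis takes the outcomes "collected at prespecified time point *t*_3_ and *t*_4_ vs. *t*_0", that is, at 3 and 6 months against baseline, and compares arms by "independent *t*-test for data normally distributed or Mann–Whitney U test for skewed data". A linear mixed model is added for change over time. The section names no analysis population. Sample Size inflates 53 per arm to 59 for 10% drop-out.

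**The concern.** Whether a patient stays in the study is made to depend on something that happens after randomisation. Everyone caught by the rule leaves before the time points at which pain is compared. Whether exclusion means from follow-up or from analysis, the result is the same: no t3 or t4 value enters the comparison. What is compared is then the patients in each arm who got through 8 weeks of daily sessions, and randomisation does not make those two groups alike.

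The loss could be related to the outcome. Tolerance of arm exercise and arm pain may well be linked, and the Discussion reports that pain intensity is negatively correlated with motor function. The arms also receive different procedures, exoskeleton training with 200 repetitions per session or conventional rehabilitation, so tolerance could differ between them. If it does, the trial could show a preventive effect that is not there or hide one that is. Outcomes that were never collected cannot be recovered at the analysis stage.

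**Working it through.** **1. The plan's own figure.** Sample Size gives 53 per arm and 10% drop-out: 53 / (1 − 0.10) = 58.9, rounded up to 59 per arm and 118 in total. This reproduces. In reverse, 59 × 0.90 = 53.1. The inflation replaces lost numbers. It does nothing about which patients are lost.

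**2. Order of events.** Randomisation, then treatment to t2 (2 months), then the comparison at t3 (3 months) and t4 (6 months). Any discontinuation of treatment therefore falls between randomisation and the outcome.

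**3. Illustration of the mechanism.** The document gives neither stopping rates by arm nor their link to pain, so every input below except the number randomised is an assumption.
- True pain proportion p = 0.35 in both arms (no treatment effect). The Introduction reports shoulder pain in 30–40% of stroke survivors.
- q = proportion of an arm that stops.
- r = how many times as likely a patient with pain is to stop as one without.
- 59 randomised per arm.

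Stopping probability without pain: q0 = q / (r·p + 1 − p). With pain: q1 = r·q0. Pain proportion among those who remain: p·(1 − q1) / (1 − q).

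Worked once, for q = 0.15 and r = 2: q0 = 0.15 / 1.35 = 0.111, q1 = 0.222, remaining proportion = 0.35 × 0.778 / 0.85 = 0.320. For q = 0.05 and r = 2: q0 = 0.037, q1 = 0.074, remaining proportion = 0.35 × 0.926 / 0.95 = 0.341. Difference: 0.021.

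| Stopping, ARAMIS vs control | r | ARAMIS remaining | Control remaining | Spurious difference | Two-sided error |
|---|---|---|---|---|---|
| any of these rates | 1 | 35.0% | 35.0% | 0 | 5.0% |
| 10% vs 10% | 2 | 33.1% | 33.1% | 0 | 5.0% |
| 10% vs 10% | 3 | 32.0% | 32.0% | 0 | 5.0% |
| 15% vs 5% | 2 | 32.0% | 34.1% | 2.1 points | 5.6% |
| 15% vs 5% | 3 | 30.3% | 33.6% | 3.3 points | 6.5% |
| 20% vs 0% | 2 | 30.8% | 35.0% | 4.2 points | 7.5% |
| 20% vs 0% | 3 | 28.3% | 35.0% | 6.7 points | 11.5% |

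The last column is a normal approximation for two proportions with 59·(1 − q) patients per arm, tested at the plan's 5% level ("1.96, according to 5% level of significance"). Swapping the arms gives the same sizes with the opposite sign. With p at 30% or 40%, the 15% vs 5% rows give 2.0–3.3 points and the 20% vs 0% rows 4.0–6.7 points.

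**4. Scale.** The planned comparison is of means (t-test or Mann–Whitney), not of proportions. The table shows how the rule can create a difference. It does not predict the bias in the planned test.

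**The case against.** The strongest case on the other side has five parts.

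- *No stated link to pain.* A reader might infer that the rule drops the patients most likely to have pain. The document does not say this. Loss of tolerance is mentioned without reference to pain, and it is not said to be the only or main reason for stopping. This objection stands: selective removal is a possibility, not a fact of the plan.
- *The rule applies to both arms.* A reader might also infer a false benefit for ARAMIS. There are no tolerance data for either arm, and control patients also have their arm mobilised in daily 60-minute sessions. With no true effect, equal and equally selective stopping gives no between-arm bias, although pain is understated in both arms. This stands too: the direction is unknown.
- *Comparison with the planned effect.* It is tempting to set the percentage points above against the 25% improvement in Sample Size. That section powers on a difference in means (6.34 against 5.4) and sets no target for pain incidence, so the comparison is not supported.
- *Other safeguards.* The CONSORT reference, the mixed model and operator-delivered treatment might be thought to cover the problem. The mixed model can at best use values recorded before exclusion. A patient who stops before t1 has only t0, when eligibility requires no pain in the affected arm. Assured adherence sits beside a 10% drop-out allowance. This part does not stand.
- *Pilot status and a condensed article.* The trial is called a pilot and exploratory, and an article may leave analysis populations to a fuller document. But the exclusion is a rule the article states, not a detail it omits, and the trial is sized and tested as a comparison of arms.

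**Conclusion.** The point holds in limited form. It is certain that the rule restricts the t3 and t4 pain comparison by a post-randomisation event, so the comparison is not as randomised; this follows from the text alone. That the rule removes patients with pain or poor tolerance, and does so differently by arm, is plausible but not shown. Under the stated assumptions the spurious between-arm difference runs from zero, through about 2–3 points at 15% versus 5% stopping, to about 4–7 points at 20% versus 0%, in either direction. These are incidence-scale illustrations with assumed rates, assumed links to pain and no true effect. They are not estimates for this trial. The rule should be changed before outcome data are lost, because it touches the primary endpoint and cannot be repaired afterwards.

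**What to change.** Replace the exclusion sentence with, for example: *Patients who discontinue the allocated treatment remain in the study, are assessed at all remaining time points through t4, and are analysed in the group to which they were randomised; a completers-only analysis is supportive.*

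Report discontinuation for intolerance by arm, using the form already planned. Some t3 and t4 values will still be missing, so state that they are handled through the planned linear mixed model, with a sensitivity analysis for data missing in relation to pain.

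The cost is a few more visits that are already scheduled, some extra analysis text, and some dilution of the estimate by non-adherence. The sample size of 118 need not change for this. No change is proposed to when or why treatment is stopped.

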### Outcomes

The effect of robot-assisted rehabilitation using ARAMIS on the prevention of the development of poststroke pain is the primary endpoint of the ROBOCOP study. The primary outcome measures consist in the assessment of pain through the VAS, including a bedside active examination and probing of somatosensory functions to test touch, temperature, and pain sensations (26). The development of neuropathic components of poststroke pain will be assessed using the DN4. The secondary endpoints include spasticity, tightly linked to pain and developed by up to 40% of patients with hemiparetic stroke, and clinical motor rehabilitation. Spasticity will be assessed using the Modified Ashworth Scale (MAS) (27) and the Resistance to Passive movement Scale (REPAS), based on the Ashworth scale (28), for major joint movements in upper and lower limbs. Clinical motor rehabilitation will be measured according to the Standardizing Measurement in Arm Rehabilitation Trials [SMART] toolbox of the recommended core set of outcome measures for rehabilitation after stroke (29, 30). The latter includes FMA-UE, the Action Research Arm Test, and the activities of daily living/stroke-specific outcomes of the Barthel Index. The clinical motor rehabilitation will also be characterized through structural and functional MRI scan. In particular, structural MRI is intended to evaluate infarct and injury volume (31) and functional MRI to assess the activation volume in the stroke ipsilateral hemisphere during movement of paretic limb, which is related to the extent of behavioral recovery (32). The connection strength between the ipsilesional primary motor cortex and the contralateral regions will be examined (33).

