**Methods:**

A total of 118 patients with hemiplegic arms due to stroke will be enrolled and randomly allocated with a 1:1 ratio to ARAMIS or conventional neurorehabilitation group. After a baseline screening at hospital discharge, ARAMIS or conventional rehabilitation will be performed for 8 weeks. The primary endpoint is the prevention of the development of poststroke pain and the secondary endpoints are prevention of spasticity and efficacy in clinical motor rehabilitation. The primary outcome measures consist in the visual analog scale and the doleur neuropatique 4 and the secondary outcome measures include: the Modified Ashworth Scale, the Resistance to Passive movement Scale; the Upper Extremity Subscale of the Fugl–Meyer Motor Assessment; the Action Research Arm Test; the Barthel Index for activities of daily living; and the magnetic resonance imaging (MRI) recovery-related parameters. After baseline, both primary and secondary outcome measures will be performed in the following time points: 1 month after stroke (*t*_1_, half of the rehabilitation); 2 months after stroke (*t*_2_, after rehabilitation); and 3 months (*t*_3_) and 6 months (*t*_4_) after stroke, critical for poststroke pain development.

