## Introduction

### Background and Rationale

Stroke represents one of the most serious causes of death and disability-adjusted life-years lost (1) destined to keep increasing due to global aging. One of the most common long-term disabilities occurring in over 69% of cerebrovascular lesions consists of impaired motor function of the upper extremities up to hemiplegia in the following 5 years in 56% of cases (2, 3). Stroke is complicated by the occurrence of poststroke pain usually within 6 months from the acute event (4), with poststroke pain syndromes reported in up to 30%−40% of stroke outliving patients (5), chronic in 11–55% of patients (6). The latter include pain caused by different pathophysiology in which nociceptive and neuropathic features can coexist ranging from pain secondary to spasticity, shoulder pain, complex regional pain syndrome (CRPS), and headache, in 1 out of 10 stroke sufferers, that is, migraine-like in 31.3% cases (7), to central poststroke pain (8). Shoulder pain is the most frequent affecting some 30–40% of stroke survivors (6). Lenticulocapsular strokes can cause hemiparesis with consequent shoulder pain (9). The development of poststroke pain correlates to the severity of stroke and paresis is associated with a 3.1-fold higher risk for stroke-related pain (10). Unfortunately, often patients suffering from pain after stroke do not find relief in current analgesic treatment because it is not supported by clinical trials, as a consequence, guidelines are lacking (9). In fact, the systematic review and meta-analysis of literature has highlighted that very few clinical trials assess the efficacy of opioids, the most potent analgesics on poststroke pain, the number of patients is very small and these studies have not been designed specifically for this condition, thus usually not evaluating the correlation between rehabilitation, pain, and physical functioning after stroke (11). Actually, stroke survivors do not even benefit from clinical trials on the novel preventative treatment of migraine, e.g., the anticalcitonin gene-related peptide monoclonal antibody eptinezumab that can provide rapid and longer-lasting action (12). This is often due to the lack of use of pain scales for an objective pain assessment validated in specific populations, e.g., patients affected by stroke, and this problem becomes even more worrying for patients with aphasia and noncommunicative and in the pandemic emergency (13–16). Robot-assisted neurorehabilitation for patients with stroke having the Integrated Robotic System for Stroke (IRSS) prototype Automatic Recovery Arm Motility Integrated System (ARAMIS) has provided a significant improvement of motor recovery (17). It consists of two computer-controlled, symmetric, and interacting exoskeletons that impress to the paretic arm the same strength and movement of the healthy arm and it has been validated in stroke survivors. The rationale for the use of ARAMIS in poststroke neurorehabilitation of the paretic upper limb relies on the possible prevention of aberrant early plasticity. According to our working hypothesis, ARAMIS might improve plasticity in agreement with the concept underlying the Reinforcement-Induced Movement Therapy (18), avoiding the occurrence of spasticity and hypotonia.

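### Infarct and injury volume is classed as a motor-rehabilitation outcome, although the lesion precedes randomisation and the protocol states no recovery rationale for it; it fits better as a t0 descriptor and covariate (minor)

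*Protocol article*

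**What the plan says.** In the protocol article, Outcomes makes motor rehabilitation a secondary endpoint and adds structural and functional MRI to its clinical scales. For the structural scan it says "structural MRI is intended to evaluate infarct and injury volume (31". For the functional scan it names activation volume during movement of the paretic limb, and says that this is related to behavioural recovery. Connection strength from the ipsilesional motor cortex is also to be examined.

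The abstract's Methods paragraph counts "the magnetic resonance imaging (MRI) recovery-related parameters" among the secondary outcome measures. Participant Timeline has primary and secondary outcomes assessed from t0 to t4. Statistical Analysis then gives one rule for all of them: "The primary (pain) and secondary (spasticity and rehabilitation parameters) outcome measures, collected at prespecified time point" t3 and t4 are set against t0 and tested by independent t-test or Mann–Whitney test at p < 0.05. A linear mixed model is added for the course over time, with no covariate named.

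The background section says "The development of poststroke pain correlates to the severity of stroke". The eligibility criteria admit lesions of any side, location and extension, and the allocation section minimises on sex only.

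**The concern.** An efficacy outcome should be something the randomised treatment is expected to move. The lesion is confirmed by imaging before enrolment and both interventions are arm exercises. The mechanism that the protocol offers is plasticity and cortical re-organisation, and nowhere does it propose a smaller lesion. If infarct volume stays among the measures of motor rehabilitation, a significant difference between arms could be reported as a rehabilitation effect with no rationale behind it.

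The same quantity measured at t0 describes the extent of the stroke, in a trial that accepts any lesion size. That makes it a natural candidate for adjustment in the pain and motor comparisons. The t-test and the Mann–Whitney test named in Statistical Analysis have no place for it.

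**Working it through.** **1. Role of the measure, section by section (protocol article)**

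| Place | Infarct and injury volume | Activation volume |
|---|---|---|
| Outcomes | listed under motor rehabilitation; no link to recovery stated | listed under motor rehabilitation; link to behavioural recovery stated |
| Abstract, Methods | not named; covered only by the general MRI item | not named; covered only by the general MRI item |
| Participant Timeline | t0 to t4 if it counts as a secondary outcome | same |
| Table 1 | no row of its own | own row, marked at t1 and t2 |
| Statistical Analysis | not named; falls under the general rule for secondary rehabilitation parameters | same |

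The comparison of infarct volume between arms thus follows from general rules and is not stated in any one sentence. No section gives the measure a baseline or severity role.

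**2. The plan's own sample size**

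Inputs from Sample Size: "1.96, according to 5% level of significance"; "0.84 for 80% power"; "primary outcome measures significant difference = 6.34 with ARAMIS and 5.4 with conventional rehabilitation (25", so the difference is 6.34 − 5.4 = 0.94. The formula uses σ, defined only as "standard deviation", with no number. The 53 per arm therefore cannot be reproduced forwards. Solving backwards:

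- n = (1.96 + 0.84)² × 2σ² / 0.94², with n = 53
- standardised difference = √(2 × 7.84 / 53) = 0.544
- implied σ = 0.94 / 0.544 ≈ 1.73

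The drop-out step does reproduce: 53 / 0.90 = 58.9, so 59 per arm and 118 in total.

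**3. What adjustment for t0 lesion volume could be worth**

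Assumption: a correlation r between t0 lesion volume and the outcome of 0.2, 0.3 or 0.4. The documents give no value.

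- residual variance = 1 − r²
- equivalent gain in patients = 1/(1 − r²) − 1
- adjusted standardised difference = 0.544 / √(1 − r²)
- power from the noncentral t distribution, 53 per arm, two-sided 5%

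| r | Residual variance falls by | Equivalent extra patients | Adjusted difference | Power |
|---|---|---|---|---|
| 0 | 0% | 0% | 0.544 | 79% |
| 0.2 | 4% | 4% | 0.555 | 81% |
| 0.3 | 9% | 10% | 0.570 | 83% |
| 0.4 | 16% | 19% | 0.594 | 86% |

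The first row is 79% and not 80% because the plan's formula uses the normal approximation.

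**The case against.** Several objections have force.

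- **No sentence says infarct volume will be tested between arms.** This is correct. With no row in Table 1, the text also fits a descriptor that helps to interpret the functional scans. But Outcomes places it under an endpoint and the general rules exempt no MRI measure, so its role needs settling either way.
- **A reader might infer that arm training cannot change infarct volume.** The documents do not address this, and the source cited for the measure is not at hand. What they support is narrower: the lesion precedes randomisation, and a link to recovery is stated for activation volume and not for infarct volume.
- **A reader might infer that the protocol itself says lesion volume predicts pain.** It does not. It speaks of stroke severity and of paresis. Taking lesion volume as a marker of severity is a further step, which is why the correlations above are assumptions.
- **A reader might infer that chance imbalance in lesion size biases the pain comparison, or would itself be tested as a treatment effect.** Neither holds. In a randomised comparison the test's type I error already covers chance imbalance, and a comparison of change from t0 largely removes a t0 difference in volume. If there is no true effect, the false-positive risk for this measure is the nominal 5% per test.
- **Covariate lists are commonly left to an analysis plan that is not shown.** That stands for the mixed model, so its lack of named covariates is not an error. The t-test and Mann–Whitney test are stated choices and take no covariate.

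**Conclusion.** The point holds in a limited form and is minor. Infarct and injury volume is placed among the measures of motor rehabilitation without a stated rationale and without a row in the schedule. A difference between arms could not be read as efficacy. That such a comparison would be made is an inference from the general rules.

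Using the t0 value as a covariate would improve the plan; leaving it out does not invalidate the tests. The size of the gain (power from about 79% to between 81% and 86%) is illustrative. It rests on assumed correlations of 0.2 to 0.4 and on a standardised difference of 0.544 solved back from 53 per arm. The validity of the primary comparison and the total of 118 are unaffected.

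**What to change.** - **Outcomes:** define infarct and injury volume as a t0 descriptor of stroke severity and not as an efficacy outcome. Keep activation volume and connectivity as the MRI outcomes.
- **Table 1:** show the structural measure at t0, so that schedule and text agree.
- **Statistical Analysis:** replace the unadjusted t-test or Mann–Whitney comparisons of pain and motor outcomes with models that include t0 lesion volume as a prespecified covariate. State the transformation. Define the volume for every stroke type enrolled, because the eligibility criteria do not restrict entry to ischaemic stroke and an infarct volume on a log scale might be undefined for some patients.

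The cost is one dropped secondary measure and one extra model term. Imaging at entry and secondary measures at t0 are already planned, so no additional visit is needed; the text should confirm that the entry imaging yields the structural volume.
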